## Patients and Methods

### General Setting

We aim to build the LIPAD cohort consisting of 1,000 participants internationally: 300 of them with *LRRK2*-PD (*LRRK2*+/PD+), 200 with pathogenic *LRRK2* variants but without PD (*LRRK2*+/PD-), 100 PD patients with pathogenic variants in PD genes other than *LRRK2* (genPD), 200 patients with idiopathic PD from the same populations (iPD; *LRRK2*-/PD+), and 200 healthy persons without pathogenic variants (HC). The majority of participants will be enrolled after genetic analysis within ROPAD (Figure 1). Extrapolating from the ROPAD findings, we expect to have a sufficient number of participants in the *LRRK2*+/ PD+, iPD, and genPD groups. Further, family members of pathogenic *LRRK2* variant carriers will be asked to participate in the LIPAD study and will be genetically tested for the familial pathogenic *LRRK2* variant. Depending on the results, they will be assigned either to *LRRK2*+/PD- or HC group. Healthy persons without pathogenic variants will be recruited from spouses of study participants or the general population. Within an anticipated 24-month recruitment period per site, ~25 centers in 10 countries on three continents will be established. Each center will have 24 months for recruitment after initiation. The majority of the centers will be those already participating in ROPAD, however, additional centers that do not participate in ROPAD but follow *LRRK2* pathogenic variant carriers will be invited to become LIPAD sites.

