### Inclusion Criteria

Recruited participants have to meet one of the following criteria: (i) clinical diagnosis of PD according to the Movement disorder Society (MDS) diagnostic criteria, (ii) first- or second-degree relative of a participant that is positive for a pathogenetic *LRRK2* variant, (iii) healthy participants with or without a family history of PD in a control group. All participants have to be above 18 years of age and have to sign an informed consent form.

Participants with the following *LRRK2* variants will be included in the *LRRK2*+ group: p.Gly2019Ser (c.6055G>A), p.Arg1441His (c.4322G>A), p.Arg1441Cys (c.4321C>T), p.Arg1441Gly (c.4321C>G), p.Asn1437His (c.4309A>C), p.Ile2020Thr (c.6059T>C), p.Tyr1699Cys (c.5096A>G).

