### Data Analysis

Data analysis will be performed at the Institute of Neurogenetics (University of Luebeck, Germany). To cover the first objective, which is the systematic characterization of PD patients and unaffected carriers with pathogenic variants in the *LRRK2* gene, we will describe the frequency of all clinical signs and symptoms including non-motor signs and the most important influencing factors such as sex, disease duration, and medication. This will result in raw and corrected frequencies with 95% confidence intervals. We will use t-tests for numerical and continuous variables and chi-square tests for categorical variables at a significance level of 0.05 for the comparisons of the clinical signs and symptoms across the groups.

For aim 2, which is to investigate the modifiers of penetrance of pathogenic *LRRK2* variants using genetic and environmental data, we will examine penetrance in logistic regression models to quantify the influence of different factors impacting penetrance.

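### Corrected frequencies are planned, but differences across the unmatched groups are tested only with t-tests and chi-square tests, which cannot carry the correction, and age is not a named factor

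*Protocol article*

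**What the plan says.** The Data Analysis section of the protocol article handles objective 1 in three steps.

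- It describes the frequency of all signs and symptoms together with "the most important influencing factors such as sex, disease duration, and medication".
- It gives the output of that step: "This will result in raw and corrected frequencies with 95% confidence intervals".
- It then names the tests: "We will use t-tests for numerical and continuous variables and chi-square tests for categorical variables at a significance level of 0.05". Their scope is "for the comparisons of the clinical signs and symptoms across the groups".

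A regression model appears only under aim 2, for penetrance.

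On the make-up of the groups:

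- The only age rule is common to all: "All participants have to be above 18 years of age" (Inclusion Criteria).
- Unaffected carriers enter through the criterion "first- or second-degree relative of a participant that is positive for a pathogenetic" LRRK2 variant.
- Controls are relatives who test negative, spouses, or people from the general population (General Setting).
- The idiopathic group is described as "200 patients with idiopathic PD from the same populations".
- No matching on age or sex is stated.
- The Discussion says that inclusion is not restricted by age at diagnosis or by medication.

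**The concern.** The article accepts that sex, disease duration and medication influence the signs, and it corrects the frequencies accordingly. The tests it names next drop that correction. A two-sample t-test and a chi-square test compare the groups as they happened to be enrolled.

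Age matters most here and is not named. Cognition, smell, autonomic function, sleep and motor scores can all be expected to vary with age. The Introduction describes penetrance as age-dependent, so unaffected carriers will tend to be younger than affected ones. Among the PD groups, disease duration can differ in the same way.

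If the plan is followed as written, a significant difference between LRRK2-PD and another PD group, or between unaffected carriers and controls, could partly or wholly reflect age. The risk grows with enrolment, because the bias stays the same while the standard error shrinks. Readers would then see adjusted frequencies next to p-values that answer a different, unadjusted question.

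**Working it through.** **The plan's own figures.** The article gives no power calculation to reproduce. The group targets add up as stated: 300 + 200 + 100 + 200 + 200 = 1,000. The Table 2 groups add up to 7 + 1 + 115 + 25 + 2 = 150.

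**Step 1: is there an age difference already?** Inputs from Table 2: idiopathic PD 63.3 (SD 10.8, n = 115); other genetic PD (genPD) 56.4 (SD 11.6, n = 25). Difference 6.9 years.

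- Pooled: variance = (114 × 10.8² + 24 × 11.6²)/138 = 119.8, SE = √[119.8 × (1/115 + 1/25)] = 2.41, t = 6.9/2.41 = 2.86, p = 0.005.
- Welch: SE = √(10.8²/115 + 11.6²/25) = 2.53, t = 2.73, p = 0.010.

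Other gaps in Table 2 (Welch):

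- LRRK2-PD (60.6, SD 9.2, n = 7) v idiopathic PD: 2.7 years younger, p = 0.48.
- LRRK2-PD v genPD: 4.2 years older, p = 0.33.
- Unaffected carriers (n = 1) and controls (n = 2) are too few to judge.

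**Step 2: what does an unadjusted test do with such a gap?** Suppose there is no genotype effect.

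- Inputs from the article: the planned group sizes, the age gaps above, and a MoCA SD of 3.3 (Table 2, LRRK2-PD and idiopathic PD; genPD shows 2.1, and one common SD is used for simplicity).
- Assumptions: a MoCA change of 0.05 to 0.10 points per year of age, which the article does not give, and a two-sided 0.05 test.
- Formulas: d = gap × slope / 3.3; SE = √(1/n₁ + 1/n₂); rejection rate = Φ(d/SE − 1.96) + Φ(−d/SE − 1.96).

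| Contrast | Gap (years) | Planned n | SE | d (slope 0.05 / 0.10) | d/SE | Rejection rate |
|---|---|---|---|---|---|---|
| Idiopathic PD v genPD | 6.9 | 200 v 100 | 0.122 | 0.105 / 0.209 | 0.85 / 1.71 | 0.14 / 0.40 |
| LRRK2-PD v genPD | 4.2 | 300 v 100 | 0.115 | 0.064 / 0.127 | 0.55 / 1.10 | 0.09 / 0.20 |
| LRRK2-PD v idiopathic PD | 2.7 | 300 v 200 | 0.091 | 0.041 / 0.082 | 0.45 / 0.90 | 0.07 / 0.15 |

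The nominal rate is 0.05 in every row.

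**Step 3: a second way to state the assumption.** For any outcome, let r be the within-group correlation with age, take an age SD of 11, and set d = r × gap / 11. With r assumed at 0.1, 0.2 and 0.3, the rates are:

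- Idiopathic PD v genPD: 0.081, 0.176, 0.336.
- LRRK2-PD v genPD: 0.063, 0.101, 0.168.
- LRRK2-PD v idiopathic PD: 0.058, 0.084, 0.127.

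Both approaches give the same picture: a modest excess for the gaps involving LRRK2-PD so far, and a marked excess for the 6.9-year gap.

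**The case against.** The other side has several good points.

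- *Correction is already planned, and the list of factors is open.* This is true. Sex and disease duration are handled descriptively, and the wording leaves room for age in the corrected frequencies. It leaves no room in a t-test or chi-square test, so the mismatch remains.
- *A reader might infer that the groups differ in age by design.* The article does not support that. One age criterion applies to every group. A difference is foreseeable from penetrance and from the recruitment of relatives, but no rule creates it.
- *A reader might infer that country confounding is established.* It is not. Idiopathic patients are to come from the same populations, some controls are spouses or relatives, and no country-by-group data are shown. With about 25 centers in 10 countries it is a plausible risk and no more.
- *A larger distortion could be quoted.* A 10-year gap with 200 per group would give 33-86% under the same slopes, but Table 2 shows no such gap for any contrast that can be judged.
- *The clearest observed gap contains no LRRK2 group.* This stands. It shows that unmatched enrolment produces age gaps. It does not show how large the gap will be in the main LRRK2 contrasts.
- *Unadjusted tests validly describe the groups as enrolled, and the article does not call them genotype effects.* This is fair, and it is why raw comparisons should be kept. But a characterization of LRRK2-PD against other groups will be read as attributing differences to the variant.
- *Which covariates serve which contrast belongs in an analysis plan.* That is true of the detail. The finding rests on the tests the article does name.

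**Conclusion.** The point holds in this form: the tests named for the group comparisons cannot carry the correction that the article plans, and age is not named. The groups are neither randomised nor stated to be matched, so the comparisons can mislead. It cannot be said that they will.

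For MoCA with an assumed slope of 0.05-0.10 points per year, the false-positive rate at the planned sizes is about 14-40% for idiopathic PD v genPD. For LRRK2-PD v idiopathic PD it is about 7-15%, with the age gap itself uncertain at n = 7. These figures assume that the gaps in the first 150 participants persist, a common SD of 3.3, and a slope that the article does not supply. Nothing can be quantified yet for unaffected carriers v controls.

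**What to change.** Replace the sentence naming the tests so that the planned correction carries through:

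- Compare groups by regression: linear for scores, ordinal for Hoehn & Yahr, logistic for the presence of a sign. Adjust for age and sex, and for country or site as a plausible confounder.
- Add disease duration only for contrasts among the three PD groups, since it is undefined for unaffected carriers and controls.
- Use medication in a sensitivity analysis among the PD groups rather than in the main model. It may reflect severity, and adjusting for it could remove real differences.
- Report adjusted differences (or odds ratios) with 95% CIs beside the raw comparisons, and name age among the factors for the corrected frequencies.

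The cost is analysis wording and programming, with no change to recruitment. Table 1 lists age, gender and medication in the eCRF. It does not list disease duration by name, so the sponsor should confirm that it can be derived from the data collected, as the article already assumes.

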### Nested Studies

All LIPAD centers can suggest nested projects, which will be coordinated by a Scientific Advisory Board. These projects can apply for external funding, will have individual ethics approvals, and can use the ROPAD/LIPAD network. The following nested studies are planned or have started at the Institute of Neurogenetics (University of Luebeck):

#### Multimodal High-Quality Magnetic Resonance Imaging (MRI)

Penetrance of *LRRK2*-linked PD depends on the age of a given individual subject. Asymptomatic carriers may, however, already demonstrate neurodegenerative changes including hyposmia, abnormal midbrain hyperechogenicity upon transcranial sonography, pathologic dopaminergic neurotransmission, structural changes of the gray and white matter, and functional reorganization of neural networks. Although first morphological and functional brain changes in pathogenic *LRRK2* variant carriers have already been identified, the overall picture is still elusive due to the relatively low number of included subjects in most studies, ascertainment biases, and variable imaging protocols. Multimodal high-quality MRI, however, is a promising secondary endpoint for clinical trials given its wide availability, cost-effectiveness, and lack of radiation.

To reveal an MRI-based biomarker for *LRRK2*+/PD+ and prodromal *LRRK2*+/PD+, we aim to acquire the following MRI modalities:

Multiparameter mapping (R1, PD^*^, MT, and R2^*^) to reveal physical tissue properties.Diffusion-weighted imaging for multicompartment diffusion models to reveal neuroinflammation and microstructural alterations.Neuromelanin imaging to reveal substantia nigra and locus coeruleus degeneration.Blood-oxygen-level-dependent functional MRI to identify changes in functional connectivity.Magnetic resonance spectroscopy to depict the mechanisms of neurodegeneration, such as involvement of energy metabolism due to mitochondrial dysfunction, which may be subject to faster change than other aspects of MR-based imaging (e.g., changes in gray matter).

#### Metabolic Studies

To investigate whether metabolic changes in *LRRK2* carriers already exist before the motor manifestation or are secondary to it, we conduct the following studies:

Energy consumption at rest using indirect calorimetry, where energy consumption is determined by measuring the air the subject breathes.Measurement of body composition, i.e., the proportion of body fat mass and lean mass, employing air displacement plethysmography. In addition, body circumference (e.g., waist and hips) and body skin folds (e.g., on the arm and waist) are measured.Measurement of physical activity and sleep behavior under everyday conditions using accelerometry. The study participants are asked to wear the accelerometer in the form of a wristwatch continuously for 7 days.

#### Genome-Wide Association Study Analysis

We will perform a genome-wide association study analysis in manifesting vs. non-manifesting carriers aimed at discovering genetic modifiers of penetrance of *LRRK2* pathogenic variants.

#### Toxicological Analyses of Household Dust

A broad non-target liquid chromatography high-resolution mass spectrometry (LC-HR-MS) screening will be performed on household dust samples collected by participants in vacuum bags [see (10)], with identification of potential toxicants of interest via the *in silico* fragmenter MetFrag (11) coupled with open chemical databases such as PubChem (12) and CompTox (13), plus specific neurotoxicity-related candidate lists and end-point information (14).

## Results

A comprehensive eCRF has been developed, consisting of an investigator-rated (1 h) and a self-rated (1.5-h) part. The questionnaires are listed in Table 1. We used validated versions of questionnaires and scales in the local languages.

**Table 1 T1:** Content of the LIPAD electronic case report form.

Demographic and general data	Genetic result, age, gender, years of education, the highest level of education, handedness, medication/treatment, medical history, family history concerning PD
PD criteria	MDS clinical diagnostic criteria for PD, absolute exclusion criteria, red flags
Clinical scores	MDS-UPDRS (Movement Disorder Society – Unified Parkinson's Disease Rating Scale) Hoehn & Yahr scale Schwab & England scale Brief smell identification test (BSIT) Montreal Cognitive Assessment (MoCA)
The self-rating part	PD risk factor questionnaire (PD-RFQ-U) Food frequency questionnaire Autonomic dysfunction (SCOPA-AUT) WHO Quality of life questionnaire (WHO-QoL) Pittsburgh Sleep Quality Inventory Epworth Sleepiness Scale Hospital Anxiety and Depression Scales

The first 10 centers across Germany and five international sites have been initiated with further centers currently undergoing ethical review (Figure 2). The first 150 participants have been enrolled (as of March 25th, 2021); Table 2.

**Figure 2 F2:**
[figure not shown]
International centers participating in LIPAD. In blue: centers with ethics approval; in black: centers in the process of receiving ethics approval.

**Table 2 T2:** Exemplary demographic and clinical characteristics of the first 150 enrolled LIPAD participants.

	***LRRK2*** **+/PD+ (group 1)**	***LRRK2*** **+/PD-(group 2)**	**iPD;LRRK-/ PD+ (group 3)**	**genPD (group 4)**	**HC (group 5)**
	***N*** **= 7**	***N*** **= 1**	***N*** **= 115**	***N*** **= 25**	***N*** **= 2**
Sex (male), *n* (%)	2 (28.6%)	0	64 (55.7%)	15 (60%)	2 (100%)
Age, mean (±SD)	60.6 (± 9.2)	40	63.3 (± 10.8)	56.4 (± 11.6)	57 (± 12)
Family history of PD, *n* (%)	3 (42.9%)	1 (100%)	19 (16.5%)	7 (28%)	1 (50%)
MDS-UPDRSIII, mean	37.7 (± 20.3)	0	34.3 (± 14.4)	28.6 (± 12.5)	4 (± 4)
(±SD), *n* complete	*N* = 3	*N* = 1	*N* = 59	*N* = 11	*N* = 2
H&Y, mean (±SD)	3 (± 0.6)	0	2.1 (± 0.6)	2.1 (± 0.7)	0.5 (± 0.5)
Schwab & England Scale, mean (±SD)	71.7 (± 21.1)	-	81.9 (± 14.7)	84.4 (± 11.2)	100 (± 0)
MoCA, mean (±SD)	25.8 (± 3.3)	29	26.6 (± 3.3)	27.6 (± 2.1)	26.5 (± 1.5)
BSIT, mean (±SD)	6.2 (± 1.7)	11	6 (± 2.6)	6.5 (± 3.3)	11 (± 1)

*H&Y, Hoehn and Yahr; MoCA, Montreal Cognitive Assessment; BSIT, Brief Smell Identification Test*.

## Discussion

LIPAD is a large-scale international scientific effort focusing on deep phenotyping of *LRRK2*-linked PD and healthy pathogenic variant carriers, including a comparison with additional relatively frequent genetic forms of PD, and with a future perspective to identify genetic and environmental modifiers of penetrance and expressivity.

The clinical assessment in LIPAD is close to the one used in the currently largest multinational cohort of genetic PD (PPMI), except for lack of collection of cerebrospinal fluid, but with the addition of an extensive questionnaire on environmental factors (15). Further, there are no restrictions on the age at diagnosis or medication for inclusion in the LIPAD study. Several other multinational prospective studies focusing on pathogenic *LRRK2* variants included only a small number of populations (4, 16, 17), revealing an important knowledge gap in multinational, standardized, genetic prospective studies, which LIPAD is aiming to close.

A comprehensive investigation of modifiers of penetrance and expressivity requires assessment of a considerable number of pathogenic variant carriers. Due to the direct enrolment of family members at an international scale, the LIPAD study will enable the analysis of modifiers of penetrance in different populations in one setting. Our recruitment strategy, mainly through the international multicenter ROPAD study, will ensure participation of a large number of *LRRK2*+/PD+ patients.

With the nested studies, which will be conducted on a subset of participants, we are aiming to provide a more in-depth phenotypic characterization especially of non-affected carriers of *LRRK2* pathogenic variants.

Currently, a complication affecting many patient studies across the world are measures imposed on personal visits to contain SARS-CoV-2 in many countries, limiting the possibility for the collection of data and biomaterials. To allow the study to proceed under these circumstances, we adjusted the protocol and procedures to collect the necessary data online. After making an online appointment, patients receive a package with patient information, informed consent forms, and a smell test by post. Then an online appointment with the study team takes place, during which the study is explained, the data is collected and the examination is performed. Study participants send signed informed consent forms and a household dust sample back to the study center by post. Biomaterials will be taken at a general practitioner's office or the study center at a later time point when study visits become possible again. The study will revert to the on-site recruitment as soon as possible after the pandemic restrictions are lifted.

LIPAD aims for a longitudinal follow-up of its study participants over a 10–15-year time period. The exact protocol is currently being developed and potential funding opportunities are being explored.

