Recently published data from the currently largest multinational prospective study that includes *LRRK2* pathogenic variant carriers, i.e., the Parkinson's Progression Markers Initiative (PPMI), provide more phenotypic details on *LRRK2* pathogenic variant carriers across international sites (6). However, as the focus of the PPMI study is predominantly on biomarkers, it does not cover environmental factors in-depth, and only includes participants with a PD diagnosis 2 years or less before enrolment who are untreated with PD medication. There remains a gap in combining phenotypic, genetic, and environmental data on *LRRK2* pathogenic variant carriers internationally, regardless of the onset of signs and symptoms and their medication status, that LIPAD is aiming to close. The objectives of the LIPAD study are (1) to provide a systematic characterization of PD patients and unaffected carriers with pathogenic variants in the *LRRK2* gene; and (2) to enable the investigation of modifiers of penetrance of *LRRK2* pathogenic variants using genetic and environmental data.

Here, we describe a protocol and a feasibility study of the first 150 participants and give a brief overview of nested studies within LIPAD. Of note, the LIPAD protocol has also been adapted to take place online due to COVID19 contact restriction measures.

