### Study Design

Upon completion of genetic screening (e.g., in ROPAD), participants are invited for a personal examination using the three-level biomaterial protocol. During a single visit, an electronic Case Report Form (eCRF) is administered and blood samples for DNA, RNA, serum/plasma, immune cell isolation, urine, and household dust for toxicological analyses are collected.

The three-level protocol was designed to accommodate available laboratory facilities at the different sites. The details of the three levels for biomaterial sampling are listed in Supporting Information Methods S2 in Supplementary Material.

In case genetic testing has not been performed before, a dried blood spot card will be sent for DNA extraction and genetic screening, as specified in ROPAD.

There are no serious safety concerns associated with the study. Participants may experience temporary discomfort during venous blood sampling and while answering the questions. However, they are instructed that they are free to omit questions they would rather not answer. There are no health risks associated with the collection of urine and house dust.

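### Affected carriers are living, prevalent cases of any disease duration, so a factor that acts on mortality more after PD onset than before it can appear as a modifier of penetrance

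*Protocol article*

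**What the plan says.** **Who enters as an affected carrier.** The Inclusion Criteria ask for a "clinical diagnosis of PD according to the Movement disorder Society (MDS) diagnostic criteria" and name no maximum time since onset or diagnosis. The Introduction makes this openness deliberate. It describes an existing biomarker cohort that "only includes participants with a PD diagnosis 2 years or less before enrolment who are untreated with PD medication", and says LIPAD will study carriers "regardless of the onset of signs and symptoms and their medication status". The Discussion adds: "Further, there are no restrictions on the age at diagnosis or medication for inclusion in the LIPAD study". That last sentence concerns age at diagnosis and medication. The missing duration limit rests on the Introduction and the Inclusion Criteria.

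**When they are seen.** Study Design: "During a single visit, an electronic Case Report Form (eCRF) is administered". The Discussion mentions follow-up over 10-15 years, but its protocol is still being developed.

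**How penetrance is analysed.** Data Analysis, aim 2: "we will examine penetrance in logistic regression models to quantify the influence of different factors impacting penetrance". The nested GWAS compares "manifesting vs. non-manifesting carriers aimed at discovering genetic modifiers of penetrance of" LRRK2 pathogenic variants. Disease duration is named in Data Analysis only as an influencing factor for the descriptive frequencies of aim 1.

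**Targets.** 300 affected and 200 unaffected carriers (General Setting).

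**The concern.** Penetrance is about whether and when a carrier develops PD. A cross-sectional sample of living carriers answers a different question: who has PD and has survived with it until enrolment. The odds ratio for affected status therefore combines two effects, one on onset and one on survival between onset and the visit. This is prevalence-incidence (survivor) bias.

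It is not reverse causation, because it also touches factors fixed before onset, such as genotype or past tobacco use. Nor is it a censoring problem: modelling age at onset among sampled carriers does not bring back affected carriers who have died.

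What is at stake is the second of the study's two objectives. The Introduction cites tobacco use as delaying onset in one carrier population. A factor that shortens life with PD would also look protective here, so a survival effect could be taken as support for such a finding.

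**Working it through.** **Plan's own figures.** The article gives no power, effect-size or survival figure for aim 2, so there is nothing to reproduce beyond the group targets: 300 + 200 + 100 + 200 + 200 = 1,000, as stated.

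**Inputs from the document.** 300 affected and 200 unaffected carriers. The 0.05 level is stated for the aim 1 comparisons; it is borrowed here and taken as two-sided.

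**Assumed inputs.** Exposure 40%; mortality after onset m = 3-5% per year; hazard ratio HR of the factor on mortality; time from onset to visit d, the same for every case; mortality in unaffected carriers u, either free of any effect of the factor or 2% per year with the same HR. The factor has no effect on onset.

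**Formulas.** Survival to the visit is exp(-m·HR·d) in exposed and exp(-m·d) in unexposed affected carriers. The log odds ratio under no onset effect is therefore -m(HR - 1)d. If the same HR acts on u in unaffected carriers over the same d years, it is -(m - u)(HR - 1)d. The standard error is √[(1/300 + 1/200)/(0.4 × 0.6)] = 0.186.

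| Case | log OR | OR | False positives at 0.05 |
|---|---|---|---|
| 3%/yr, HR 1.2, 5 y, no effect in unaffected | -0.03 × 0.2 × 5 = -0.03 | 0.97 | 5.3% |
| 3%/yr, HR 1.5, 10 y, no effect in unaffected | -0.03 × 0.5 × 10 = -0.15 | 0.86 | 12.7% |
| 5%/yr, HR 1.5, 10 y, no effect in unaffected | -0.05 × 0.5 × 10 = -0.25 | 0.78 | 26.9% |
| 3%/yr, HR 1.5, 10 y, same HR on 2%/yr | -0.01 × 0.5 × 10 = -0.05 | 0.95 | 5.8% |
| 5%/yr, HR 1.5, 10 y, same HR on 2%/yr | -0.03 × 0.5 × 10 = -0.15 | 0.86 | 12.7% |
| 5%/yr, HR 2, 10 y, no effect in unaffected | -0.05 × 1 × 10 = -0.50 | 0.61 | 76.5% |
| 5%/yr, HR 2, 10 y, same HR on 2%/yr | -0.03 × 1 × 10 = -0.30 | 0.74 | 36.3% |

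The direction reverses for a factor that prolongs survival: 3%/yr, HR 0.5, 10 y gives log OR +0.15, OR 1.16.

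**Does age adjustment remove it?** Lifetimes of carriers aged 40-85 were simulated, with a factor in 30% of them that does not affect onset and an assumed mean survival of 15 years under the excess mortality of PD. Age-adjusted logistic regression in the living gave OR 0.99 with no survival effect, 0.80 when the factor raised PD-related mortality by HR 1.5, and 0.66 at HR 2. When the factor doubled background mortality alike before and after onset and left the PD excess alone, the OR was 1.02: equal absolute effects cancel. In a second model, with PD multiplying background mortality by 2.5, the OR was 0.76 if the factor doubled mortality only after onset and 0.86 if it doubled mortality both before and after.

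**What a recent-onset analysis would do.** With onset within 5 years (mean 2.5 years assumed), 5%/yr and HR 2, the log OR is -0.05 × 1 × 2.5 = -0.125, OR 0.88 instead of 0.61. With an assumed 100 such cases against 200 unaffected carriers, the standard error is √[(1/100 + 1/200)/0.24] = 0.25.

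**Can a duration contrast classify factors?** Assume 100 cases in each of two strata with mean durations of 2.5 and 15 years. For HR 1.5 and 3-5%/yr the contrast is 0.03 × 0.5 × 12.5 = 0.19 to 0.05 × 0.5 × 12.5 = 0.31, with standard error √[(2/100)/0.24] = 0.289. The chance of detecting it is 10% to 19%.

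**The case against.** **This belongs in the analysis plan.** Aim 2 has one sentence in a condensed article, nothing there excludes an analysis by duration, and the open eligibility is deliberate and explained. This stands as a reason not to touch eligibility. It does not dispose of the point, because the article itself fixes the sampling, the outcome and the reading of the result as penetrance.

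**Not every factor that changes survival is affected.** A reader might infer that any such factor will show up as a modifier. That goes too far: equal absolute effects on mortality before and after onset cancel. Tobacco is a case in point. It would be expected to act on mortality in both groups, so the figures that leave unaffected carriers untouched are an upper case for it.

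**The size is assumed.** This stands in full. Only 300 and 200 come from the article. The Introduction describes LRRK2-linked PD as apparently milder in motor and cognitive function, which lends no support to large excess mortality.

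**The rates do not carry over to the GWAS.** Also correct. At an assumed threshold of 5 × 10⁻⁸ even the strongest case above (OR 0.61) is declared significant only about 0.3% of the time. The bias in the estimate remains; the false-positive rates do not.

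**The consequence is indirect.** The objective is worded as enabling the investigation of modifiers, and follow-up is intended. No text says that a later trial would act on these odds ratios, so that inference is not made here.

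**Conclusion.** The point holds in a limited form. As described, the sampling and the models mix effects on onset with effects on survival after onset, and age adjustment did not separate them in simulation. The factors at risk are those whose absolute effect on mortality is larger after onset than before.

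In the middle case (HR 1.5, 10 years, 3-5% per year after onset, 40% exposure) a true odds ratio of 1 moves to 0.86-0.78 if mortality in unaffected carriers is untouched by the factor, and to 0.95-0.86 if the same hazard ratio acts on 2% per year there. False positives at 0.05 are 13-27% and 6-13%. For weak effects the bias is negligible. All survival inputs are assumptions, so the documents show that the bias can arise and in which direction, but not that it is large. An added sensitivity analysis is a proportionate response; a change of design is not called for.

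**What to change.** Keep eligibility and the all-carrier logistic model. Add to the analysis plan, for aim 2 and for the leading GWAS hits:

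- A pre-specified, age-adjusted sensitivity analysis comparing recent-onset affected carriers (for example 5 years or less since onset) with unaffected carriers, reported beside the all-carrier estimate and the estimate by disease duration.
- A rule of interpretation: where the recent-onset estimate is materially weaker or differs in direction, call the factor a penetrance modifier only with the caveat that survival after onset may contribute.
- A statement that a non-significant trend with duration does not rule this out. At 10-19% power for the middle case, the trend cannot serve to classify factors.

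**Cost.** A few lines of text. Disease duration is already named for aim 1, so its use would be extended to aim 2. The recent-onset intervals are wider (standard error about 0.25 against 0.19 with an assumed 100 cases), and the bias is reduced but not removed.
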